### Recruitment and informed consent

Pharmacists, after having assessed patients’ eligibility for the study, will provide an information letter and consent form to each patient, who will be given an opportunity to consider their participation. All signed consent forms will be retained by the pharmacist in the pharmacy.

### Procedures

#### Pharmacist randomisation and blinding

An academic member of staff at Medway School of Pharmacy, experienced in clinical trials will be in charge of the randomisation process. Pharmacists will be randomly allocated to group A or B. Pharmacists will be stratified by location, prior to randomisation, using computer-generated random numbers. Blinding will not be possible either at pharmacist or patient level because the nature of the intervention requires their full knowledge. However the PI, as assessor of the main outcome measure, severity of asthma, will remain blind throughout. As group allocation will be intrinsic to the data gathered for each patient, in order to maintain blindness, the PI will access the data only after all patients have been followed up at three months (see Figure 1).

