### Pharmacist training

Training sessions will last for a half day and will be provided in each region by the PI, a fully trained and qualified pharmacist accredited to provide MURs in England since 2005. The training supports the development of pharmacists’ clinical skills and knowledge using question and answer sessions, mock interviews and role-play. The training material was developed and evaluated during earlier work. Contributions to the training will also be included from local respiratory consultants and general practitioners who will cover asthma management, physiopathology, medical conditions, different treatments according to asthma severity and GINA guidelines. Pharmacists from Groups A and B will be trained at different times. The use of the ACT test will be explained to both groups before T0 but only group A will receive the I-MUR training at this time point; group B will receive this training just before T3.

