### ACT

The ACT (primary outcome measure) is a patient-completed questionnaire with five items assessing asthma symptoms (daytime and nocturnal), use of rescue medications, and the effect of asthma on daily functioning. Each item includes response options corresponding to a 5-point Likert scale, which are summed to yield a score ranging from 5 (poor asthma control) to 25 (complete asthma control). Schatz et al. [27] found that a cut off score of 19 or less identifies patients with poorly controlled asthma.

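### The PI cannot stay blind as the protocol states: the PI trains the two groups separately, and the data-access rule permits access before T9

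*Protocol article*

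**What the plan says.** The section on pharmacist randomisation and blinding first concedes that neither pharmacists nor patients can be blinded. It then offers one protection: "However the PI, as assessor of the main outcome measure, severity of asthma, will remain blind throughout". It recognises a difficulty, "As group allocation will be intrinsic to the data gathered for each patient", and answers it with a rule on data access: "in order to maintain blindness, the PI will access the data only after all patients have been followed up at three months".

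The section on pharmacist training says: "Training sessions will last for a half day and will be provided in each region by the PI". It continues: "Pharmacists from Groups A and B will be trained at different times". Both groups have the ACT explained to them before T0, but "only group A will receive the I-MUR training at this time point; group B will receive this training just before T3".

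The ACT section describes the outcome itself: "The ACT (primary outcome measure) is a patient-completed questionnaire". The pharmacist administers it in the consultation area. The data analysis section places an interim analysis after T6, when every patient has three months of follow-up after the intervention, and the final analysis after T9. The sample size section counts T3, T6 and T9 among the ACT comparisons with baseline.

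**The concern.** A blinded assessor is the only blinding the protocol claims. Someone appraising the trial would give credit for it, particularly because the outcome is self-reported and everyone else knows the allocation. If the person named as blind learns the groups through another duty in the same plan, the trial lacks a property that it states.

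What is at stake is the accuracy of the blinding claim and, to a lesser degree, decisions on conduct and analysis that may be taken in knowledge of the groups. The article leaves room for such decisions. It mentions a percentage change in ACT score and a cut-off at 19/20, several time points, groups taken separately and combined, and results by region.

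**Working it through.** No sample size, power or alpha figure enters this point. The check sets the sections side by side and compares the timeline with the claim.

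**1. Does the training reveal allocation?**
- Trainer: the PI, in each region (pharmacist training). Local respiratory consultants and GPs contribute content, but no other trainer is described for I-MUR.
- Timing: Group A is trained in I-MUR before T0, and Group B just before T3.
- Consequence: attendance at a session identifies the group. The PI can know Group A before T0 and, by T3, the allocation of all 360 planned pharmacists. The pharmacist is the cluster, so this is the full allocation list.
- The only safeguard offered, delayed access to data, does not act on this route.

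**2. Does the data-access rule keep the PI blind to the end?**
- The protocol itself says that the data show the group.
- Release point: "the PI will access the data only after all patients have been followed up at three months".
- Group A receives I-MUR at T0, so its three-month follow-up falls at month 0 + 3 = T3.
- Group B receives I-MUR at T3, so its three-month follow-up falls at month 3 + 3 = T6.
- All patients have therefore reached it at T6, which agrees with the data analysis section.

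| Reading of the release point | Earliest access | Gap to the last ACT (T9) |
|---|---|---|
| Three months after the intervention | T6 | 9 − 6 = 3 months |
| Literally month three of the study | T3 | 9 − 3 = 6 months |

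On either reading, access is permitted before the T9 ACT is collected. On the likelier reading, one of the three follow-up assessments is still outstanding.

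**3. Could a blind PI have protected the measurement?**
- The patient completes the ACT, the pharmacist administers it, and pharmacists upload the trial data. The protocol says that pharmacists and patients are unblinded.
- The document describes no step at which the PI scores or adjudicates the ACT. Calling the PI its assessor is therefore doubtful, and even perfect blinding of the PI would leave the measurement open-label.

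**The case against.** Several points on the other side are sound and limit the finding.

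- **Withholding the data does protect something.** A reader might infer that the plan has no safeguard at all. That goes too far. If release is at T6, the contrast at T3 between treated and not-yet-treated patients has been fully collected before the PI sees any outcome. Knowing who was trained is not the same as seeing outcomes by group.
- **The rule sets an earliest date, not a scheduled opening.** A reader might infer that the PI will open the data before T9. The text permits this and the interim analysis makes it likely, but it is not stated. The flow diagram cited for this rule is not shown.
- **No analyst is named.** It is tempting to say that someone who knows the groups will choose the analysis. The article does not say that the PI runs either analysis, and an analysis plan that is not shown may fix those choices.
- **The open-label status is disclosed.** The protocol says plainly that pharmacists and patients are not blinded, so it cannot be accused of hiding this. Patients also have privacy and time to complete the ACT, which partly limits the pharmacist's influence.

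None of this rescues the statement itself. Even if the PI waited until after T9 to open the data, the training would already have revealed the allocation.

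**Conclusion.** The concern holds as a contradiction within the protocol. The claim that the PI stays blind for the whole trial conflicts with the PI's role as trainer, and this ground alone is enough. The timing of data access is a second, weaker ground. It rests on reading the three-month follow-up together with the data analysis section, though the literal alternative would put access earlier still.

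The practical consequence is limited. Measurement of the ACT is unaffected, because the PI has no described part in it, and collection of the T3 contrast is shielded if release is at T6. What remains is a possible influence on conduct and on analysis decisions, mainly for the T9 data. A reader might want to express this as a fraction of the effect the trial is sized for. The document gives no basis for such a figure, and reporting bias in the ACT would come from unblinded patients and pharmacists, not from what the PI knows.

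The conclusion assumes that the PI delivers the I-MUR training to both groups, as the training section says.

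**What to change.** Replace the sentence on the PI's blinding with a statement that the ACT is patient-reported and open-label, and that the PI is aware of allocation through the training. This correction is needed whatever else is done.

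If any blinding is to be claimed, confine it to the analysis. The academic in charge of randomisation would export the ACT data for the between-group comparisons, including T6 and T9 where they are compared, with recoded pharmacist identifiers and a dummy group label. The I-MUR fields would be left out, because they show when the service was given. The planned analysis would be run on that file before the label is broken. Masking of this kind is imperfect, since a clear difference in the timing of improvement could suggest which group started early. It would still be a claim that the design can support.

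The cost is a change of wording and one recoded export by existing staff. Recruitment, visits and sample size do not change.

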**Figure 1 Fig1:**
[figure not shown]
Flow diagram for the study (Adapted from BMJ 2012; 345:e5661 doi:10.1136/Bmj.e5661, September 2012).

### Pharmacist training

Training sessions will last for a half day and will be provided in each region by the PI, a fully trained and qualified pharmacist accredited to provide MURs in England since 2005. The training supports the development of pharmacists’ clinical skills and knowledge using question and answer sessions, mock interviews and role-play. The training material was developed and evaluated during earlier work. Contributions to the training will also be included from local respiratory consultants and general practitioners who will cover asthma management, physiopathology, medical conditions, different treatments according to asthma severity and GINA guidelines. Pharmacists from Groups A and B will be trained at different times. The use of the ACT test will be explained to both groups before T0 but only group A will receive the I-MUR training at this time point; group B will receive this training just before T3.

### Study timeline

The planned duration of the study is nine months.

### ACT

The ACT (primary outcome measure) is a patient-completed questionnaire with five items assessing asthma symptoms (daytime and nocturnal), use of rescue medications, and the effect of asthma on daily functioning. Each item includes response options corresponding to a 5-point Likert scale, which are summed to yield a score ranging from 5 (poor asthma control) to 25 (complete asthma control). Schatz et al. [27] found that a cut off score of 19 or less identifies patients with poorly controlled asthma.

#### How will the ACT test be administered?

Pharmacists will administer ACT tests to their patients in the pharmacy consultation area allowing patients’ privacy to read the questions and take the necessary time to respond.

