**Methods/Design:**

This is a cluster randomised controlled trial of the I-MUR service. Data will be collected over time before, during and after pharmacists’ intervention. Fifteen Italian regions will be involved and it is aimed to recruit 360 community pharmacists and 1800 patients. Each pharmacist will receive training in medicines use review, recruit five patients, administer the Asthma Control Test and provide the I-MUR service. Pharmacists will be allocated to different groups, one group will be trained in and provide the I-MUR service immediately after completion of the baseline ACT score, the other group will receive training in the I-MUR and provide this service three months later. Group allocation will be random, after stratification by region of Italy. The I-MUR service will involve gathering data following each patient consultation including demographic details, patients regular medications, including those used for asthma, their attitude towards their medications and self-reported adherence to treatments. In addition, pharmacists will identify and record pharmaceutical care issues and any advice given to patients during the I-MUR, or recommendations given to doctors. Pharmacists will upload trial data onto a web platform for analysis. The primary outcome measure is the severity of asthma before, during and after the I-MUR assessed using the Asthma Control Test score. Secondary measures: number of all active ingredients used by patients during and after the I-MUR, number of pharmaceutical care issues identified during the I-MUR, patients’ self-reported adherence to asthma medication during and after the I-MUR, healthcare costs based on the severity of asthma, before, during and after the I-MUR service provision.

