### Italian medicines use review (I-MUR)

This study is about developing a similar service in Italy where no such services exist. The I-MUR has been designed as a structured interview, supported by a quantitative questionnaire enabling pharmacists to capture in a systematic way a patient’s demographic data, quantity and type of medicines used, their knowledge about the medicines used, their adherence to the medicines, actual complaints (e.g. shortness of breath, chest tightness, night time waking, need for rescue medicines, limitation on activity including exercise), plus any pharmaceutical care issues identified by the pharmacists, the advice given to physicians and to patients, including healthy living advice, using an online platform (Qualtrics®).

The Italian government is considering introducing the I-MUR service, but at present there is no evidence from Italy on the feasibility, acceptability or effectiveness of such a model. Hence there is a need to gather robust data on all aspects of the potential new service to inform service design and delivery.

A pilot study was carried out between October 2012 and January 2013, to assess the feasibility of Italian community pharmacists delivering I-MURs to patients with asthma [21]. In this phase, the MUR template used in England was adapted and supplemented with a structured interview to be conducted with patients. The template also included the classification of pharmaceutical care issues (PCIs) which were potentially identifiable by pharmacists during the patient consultation. Pharmaceutical care issues were classified using the method developed by Krska et al. [22] where they are defined as “an element of a pharmaceutical need which is addressed by pharmacists”. This enabled pharmacists to categorize, using a systematic approach, all issues they found during the consultation.

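### The primary ACT is collected by the unblinded pharmacist who delivers the I-MUR, so reporting may differ between groups at T3, the only randomised comparison with no I-MUR

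*Protocol article*

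**What the plan says.** All references are to the protocol article.

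- **Roles.** The abstract (Methods/Design) has each pharmacist "recruit five patients, administer the Asthma Control Test and provide the I-MUR service". It adds: "Pharmacists will upload trial data onto a web platform for analysis".
- **Outcome.** The ACT section states: "The ACT (primary outcome measure) is a patient-completed questionnaire with five items". The items cover daytime and night symptoms, rescue medication and daily functioning, and the total runs from 5 to 25.
- **Administration.** The section on how the ACT is administered says: "Pharmacists will administer ACT tests to their patients in the pharmacy consultation area". It gives patients privacy while reading and time to respond. It does not say who receives the completed form or who enters the answers.
- **Blinding.** Pharmacist randomisation and blinding states: "Blinding will not be possible either at pharmacist or patient level because the nature of the intervention requires their full knowledge". It continues: "However the PI, as assessor of the main outcome measure, severity of asthma, will remain blind throughout". The method is to withhold the data from the principal investigator until the three-month follow-up of all patients is complete.
- **I-MUR content.** The I-MUR section lists, among the things the interview captures, "actual complaints (e.g. shortness of breath, chest tightness, night time waking, need for rescue medicines, limitation on activity including exercise".
- **Timing.** Planned intervention places the I-MUR after the ACT, at T0 in one group and at T3 in the other. Data analysis compares scores between groups at every time point.

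**The concern.** Treatment cannot be blinded here, and the article says so openly. Who collects the outcome is a separate choice, and the article leaves it with the treatment provider.

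At T3 the groups differ in more than asthma control. A Group A patient completes the ACT for a pharmacist who has already gone through breathlessness, night waking, rescue use and activity limits with them. A Group B patient has not had that conversation, because the Group B I-MUR follows the T3 ACT. Patients may answer differently after it, whether or not their asthma has changed. After T3 both groups have had the service, so no later visit gives a randomised comparison with no I-MUR.

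The one blinding measure does not reach this problem. The principal investigator is called the assessor, but the score comes from the patient, and delayed access cannot affect answers already given.

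The article excludes spirometry (Strengths and limitations), so there is no objective lung-function measure to set beside the ACT. The cost outcome is estimated from asthma severity, so a reporting shift would carry into it.

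**Working it through.** **Step 1. Reproduce the planned sample size.** Inputs from Proposed sample size and Table 1, option D: alpha 0.05 (two-sided assumed, as sidedness is not stated), power 95%, ICC 0.02, 4 patients per pharmacist, d = 20%, 693 patients per group.

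- Unclustered n per group = 2 × (1.960 + 1.645)² / 0.20² = 650, reading d as 0.20 SD.
- Design effect = 1 + (4 − 1) × 0.02 = 1.06.
- Clustered n = 650 × 1.06 = 689, against 693 stated. Power at 693 is 95.1%.

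Options A, B and C also reproduce on this reading (568, 558 and 702 against 575, 560 and 700). Reading d as 20 percentage points, over four illustrative pairs of rates, gives only about 116 to 180 per group. So the trial is in effect sized for 0.20 SD.

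**Step 2. Precision of the T3 difference, in SD units.**

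- SE = √(2 × 1.06 / 693) = 0.055.
- Smallest significant difference = 1.96 × 0.0553 = 0.108.

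**Step 3. Chance of a significant T3 difference with no true effect.** Suppose reporting alone shifts the Group A mean by b, in either direction. Then P = Φ(b/SE − 1.96) + Φ(−b/SE − 1.96).

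| Assumed shift b (SD) | P(significant) |
|---|---|
| 0 | 5% |
| 0.05 | 15% |
| 0.10 | 44% |
| 0.15 | 77% |
| 0.20 | 95% |

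**Step 4. The same in ACT points.** The article gives no SD for the ACT, so 3, 4 and 5 points are assumptions.

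| Assumed SD (points) | Design effect size, 0.20 SD | Smallest significant difference, 0.108 SD | P(significant) for a 0.5-point shift |
|---|---|---|---|
| 3 | 0.6 | 0.33 | 85% |
| 4 | 0.8 | 0.43 | 62% |
| 5 | 1.0 | 0.54 | 44% |

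These figures show how little shift would matter. They do not estimate the shift that would occur.

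**Step 5. Do the stated safeguards cover this route?**

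| Safeguard | What it covers | What it leaves open |
|---|---|---|
| Privacy and time to respond | Pressure while the patient answers | Whether the pharmacist then sees or keys the answers |
| Delayed access for the principal investigator | Influence of the principal investigator before follow-up is complete | Patients and pharmacists, who produce and handle the score |
| ACT before the I-MUR at the treatment visit | Same-day influence of the consultation | The Group A consultation three months before T3 |

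**The case against.** The strongest reply is that the ACT is self-completed, has fixed response options that are simply added up, and is answered in private. No section says that the pharmacist reads the completed form. That is inferred from the pharmacist administering the test and uploading the data, and a condensed article may leave form handling to the full protocol. This stands, and it is why the point is a risk and not a demonstrated bias.

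A reader might infer more than the article supports:

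- **That Group A scores will be inflated to please the pharmacist.** Nothing shows this. Talking through night waking or rescue use could equally make patients notice symptoms and score lower.
- **That pharmacists will enter scores leniently.** Adding five ticked options needs no judgement, and nothing suggests misrecording.
- **That professional interest favours Group A.** The Discussion links a positive result to new prospects for the profession, but pharmacists in both groups volunteered and will provide the service. That interest does not separate the groups; prior I-MUR contact does.
- **That the bias can be shown to equal the planned effect.** One can always choose a share of patients and a shift per item that multiply to that size. Such a scenario has no source in the article.

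The article is also partly open about the problem. It states the lack of blinding, the absence of spirometry and the possibility that the ACT may prove unsuitable as a primary outcome. It does not name reporting that differs between groups, and it presents the principal investigator as blinded assessor. That part of the point is unaffected.

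**Conclusion.** The point holds as a risk of bias that can be partly avoided. The article supports three things: the unblinded provider administers the primary outcome and uploads the data; T3 is the only randomised contrast of I-MUR with no I-MUR; and the blinding claimed for the principal investigator does not protect a patient-reported score.

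Direction and size are unknown. Sensitivity is known given the plan's own inputs: about 0.11 SD reaches significance at T3, and an assumed reporting shift of 0.10 SD with no true effect would do so about 44% of the time, against a nominal 5%. This rests on a simple two-sided comparison of T3 means with 693 evaluable patients per group and ICC 0.02. The large sample does not protect against such a shift; it makes a small one easier to detect as if it were an effect. No sample-size figure is wrong on this account. A cheap improvement is available and should be made.

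**What to change.** 1. Have patients submit the ACT directly on the web platform already in use, under their study code, or return it in a sealed paper form. The pharmacist should neither see nor key the answers. Apply this identically in both groups and at T0, T3, T6 and T9. The existing order, ACT before I-MUR, needs no change.
2. Reword Pharmacist randomisation and blinding so that the principal investigator is no longer presented as blinded assessor of the ACT. Say that patients report the outcome unblinded and that the principal investigator's access to the data is delayed.
3. In Strengths and limitations, state that reporting may differ between groups at T3 because patients know whether they have had the I-MUR.

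**Cost.** A change to the web form and revised instructions to the pharmacists, with any ethics notification this requires. Internet access where the consultation takes place is already an inclusion requirement, but a device for the patient is not, so a paper fallback is needed. Expect some missing items and a mix of completion modes; recording the mode would allow it to be checked. No extra staff are needed. The change removes the pharmacist's view and entry of the answers. It does not remove patient unblinding, which is why item 3 is still needed.
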